### Qualitative research informing the design of the interventions

All assessment and intervention materials will be pilot tested with seniors in a different region of Germany than the intervention and assessment sites to prevent spill-over effects. A four-week pilot intervention and a focus group interview will be conducted. During this pilot, participants will be asked whether they are satisfied with the support received during the intervention period and with the comprehensibility and difficulty of the exercise brochures. Focus groups with participants who receive Fitbit Zips to objectively track PA in the second intervention arm will be conducted to assess the usability of the Fitbit Zips. Adaptations to all intervention materials and the website will be made based on the results of these pilot tests.

### Analytic strategy

#### Quantitative analysis, sample size

Hierarchical linear regression models will be used to analyze the intervention effects. Due to the week-wise randomization scheme, recruitment week will be included as a clustering variable. Change over time in objectively measured PA will serve as the primary outcome variable. Change over time will be calculated by subtracting the baseline value from the follow-up value (PA_T1_-PA_T0_). To assess the intervention effects, two dummy variables for intervention groups 1 and 2 will be added contrasting the change over time in PA in each intervention arm with the changes in the delayed intervention control group. Expecting small to moderate intervention effects [45], we calculated the sample size assuming a standardized mean difference of 0.33 in change over time between the intervention groups and the delayed intervention control group. Further, assuming ten clusters (recruitment weeks) per study arm and an intraclass correlation of 0.01, 190 participants per study arm will be necessary for the analysis with α = 0.05 (two-sided test) and β = 0.20. Expecting a loss to follow-up of 20%, we aim for a sample size of *n* = 684 at baseline.

Changes in cardiovascular fitness, physical performance, body fat, cognitive dysfunction, fear of falling, and quality of life will be analyzed as secondary outcomes. Several variables will be included as potential confounders, such as baseline PA-level, age, gender, education, motivational stage, and other health behaviors. In additional analyses, the moderating influence of gender, socioeconomic strata, and motivational stage on intervention effects will be explored.

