Because a large body of evidence indicates that tailoring of intervention materials and messages to participants’ characteristics, such as gender, PA level at study entry, and readiness to engage in PA, is associated with greater success in achieving PA goals in the long-term [20, 22–26], intervention materials employed in the majority of the interventions in the above cited studies used tailoring. However, although a wide range of PA interventions is available in Germany [27], only few are tailored to characteristics and needs of older adults or readiness to engage in PA and the majority of studies investigating effects of PA interventions in this population demonstrated rather small behavioral changes [25]. Furthermore, the effects of self-monitoring of PA behavior via web-based diaries, logs or tracking devices have, thus far, not been systematically investigated in older populations in Germany.

Therefore, the main aim of the current study is to compare the effectiveness of two different web-based interventions (encouraging subjective vs. subjective and objective PA self-monitoring) among older adults living in five communities in the Bremen-Oldenburg metropolitan region to a delayed intervention control group. Recommendations regarding PA and intervention materials provided to participants of both web-based interventions will be tailored to gender, PA-level, and stage of readiness to engage in the interventions assessed at baseline. The study is embedded in the larger Physical Activity and Health Equity: Primary Prevention for Healthy Ageing (AEQUIPA) research network which is funded by the Federal Ministry of Education and Research (BMBF).

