### Study aims

The following main research question will be examined in this study:Is a web-based intervention with subjective and objective PA monitoring more effective for the promotion of PA among older adults than a web-based intervention with subjective PA monitoring only compared to a delayed intervention control group?

Secondary research questions of the study are the following:Do participants’ characteristics (e.g., age, gender, motivational stage) influence intervention attendance and PA behavior?Is participation in the web-based interventions associated with improvements in secondary outcomes, such as well-being, quality of life, fear of falling, physical and cognitive functioning?

An additional objective of the study is to improve our understanding of how web-based interventions and technologies for PA tracking ought to be designed to be usable for the target group and which features ought to be included from the user’s point of view.

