### Expected results

We expect to find more pronounced increases in PA and the secondary outcomes in the two intervention arms (intervention groups 1 and 2) compared to the delayed intervention control group, as well as more pronounced intervention effects in persons in intervention group 2 compared to intervention group 1. We base this assumption on previous trials conducted in the United States and other parts of Europe demonstrating significant increases in PA in persons participating in web-based interventions for PA promotion compared to control groups (e.g., [18, 21, 26, 47, 48]).

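### The main research question sets group 2 against group 1, but the analysis section specifies and sizes only the contrasts of each intervention group with control

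*Protocol article*

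**What the plan says.** Four parts of the protocol article bear on the primary comparison.

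- **Study aims.** The one main research question asks whether subjective plus objective monitoring is "more effective for the promotion of PA among older adults than a web-based intervention with subjective PA monitoring only". The comparator after the word *than* is group 1. The sentence then ends by also naming the delayed intervention control group, so its grammar is unclear.
- **Expected results.** Both intervention groups are expected to improve more than control. In addition the authors expect "more pronounced intervention effects in persons in intervention group 2 compared to intervention group 1".
- **Abstract and Background.** Here the aim is each intervention against control. The Background says "the main aim of the current study is to compare the effectiveness of two different web-based interventions" and completes the sentence with the delayed intervention control group as comparator.
- **Quantitative analysis, sample size.** In the hierarchical model "two dummy variables for intervention groups 1 and 2 will be added contrasting the change over time in PA in each intervention arm", and the sentence names the delayed intervention control group as the comparator for both. The sample size rests on a "standardized mean difference of 0.33 in change over time between the intervention groups and the delayed intervention control group", "assuming ten clusters (recruitment weeks) per study arm and an intraclass correlation of 0.01", two-sided α of 0.05 and β of 0.20, giving 190 per arm for analysis.

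No section names a contrast of group 2 with group 1, a difference between them to detect, or power for one.

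**The concern.** The article fixes the outcome, model, coding, effect size, α and power, so the analysis it describes can be set against the question it calls main. The two do not match. Two contrasts with control show whether each intervention beats waiting. Neither shows whether adding the tracker beats the diary alone.

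Two results would leave the question open. If both arms differ significantly from control, no planned quantity says whether they differ from each other. If only one does, a reader may take that as evidence of a difference between the interventions, although a significant and a non-significant result can lie close together. A contrast added after the results are known would be post hoc for a question stated as the main one.

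**Working it through.** **1. Setting the sections side by side**

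| Section | Comparison stated |
|---|---|
| Abstract, Background | each intervention vs control |
| Study aims, main research question | group 2 vs group 1, with control also named |
| Expected results | each intervention vs control, and group 2 vs group 1 |
| Quantitative analysis, model | group 1 vs control; group 2 vs control |
| Quantitative analysis, sample size | intervention vs control only |

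One could read the Study aims sentence as asking whether group 2's gain over control exceeds group 1's gain over control. The quantity is then (group 2 − control) − (group 1 − control) = group 2 − group 1, so that reading leads to the same unspecified contrast.

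**2. Reproducing the stated sample size (one arm vs control)**

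Inputs from the sample size paragraph: difference d = 0.33 SD, k = 10 recruitment weeks per arm, intraclass correlation 0.01, n = 190 per arm, two-sided α = 0.05.

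- Cluster size m = 190/10 = 19.
- Design effect = 1 + (19 − 1) × 0.01 = 1.18.
- Standard error of a difference between two arms, in SD units = √(2 × 1.18/190) = 0.1114.
- Non-centrality = 0.33/0.1114 = 2.96.
- Degrees of freedom = 2 × (10 − 1) = 18; critical t = 2.101.
- Power from the non-central t = 0.7996.

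The stated 190 per arm therefore reproduces. A normal approximation would give 0.842 at 190 per arm and would need only about 170, so the t calculation appears to be the one used.

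**3. The same design applied to group 2 vs group 1**

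The arms are of equal size, so the standard error is again 0.1114. The article gives no expected difference between the two interventions, so the values below are assumptions shown as a range.

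| Assumed group 2 − group 1 (SD) | d/0.1114 | Power, 18 df | Power, 27 df |
|---|---|---|---|
| 0.10 | 0.90 | 13.6% | 13.9% |
| 0.15 | 1.35 | 24.7% | 25.5% |
| 0.20 | 1.79 | 39.7% | 40.9% |
| 0.25 | 2.24 | 56.5% | 58.0% |
| 0.33 | 2.96 | 80.0% | 81.4% |

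The last column uses all 30 weeks of the three-arm model (30 − 3 = 27 df). It changes little. For 80% power, group 2 would have to exceed group 1 by the whole effect assumed for an intervention over control. If group 1 reaches the planned 0.33, group 2 would need 0.33 + 0.33 = 0.66 against control.

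**4. Why two tests against control do not settle the question**

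A contrast is significant when the observed difference exceeds 2.101 × 0.1114 = 0.234 SD. Suppose group 1 shows 0.20 against control (not significant) and group 2 shows 0.27 (significant). The difference between them is 0.07, with a 95% interval of 0.07 ± 0.234, or −0.16 to 0.30. One significant and one non-significant result would then sit alongside no evidence that the interventions differ.

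**The case against.** Much of the other side stands.

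- **The aim is not uniformly head-to-head.** The Abstract and Background name control as comparator, the Study aims sentence ends with control, and the analysis matches the Abstract and Background. It would be too strong to say that the trial's aim goes untested. What stands is that the sections disagree and that the question labelled main has no planned contrast.
- **The model can answer it.** A reader might infer that the question could only be settled by comparing two p-values against control. That is wrong: two dummy variables with a common reference identify all three pairwise differences. The gap is one of specification.
- **No power claim is false.** A reader might also infer that the article claims 80% power for group 2 against group 1. It does not, because the 0.33 is tied to intervention versus control. Sizing a trial for active versus control and accepting less power between active arms is a legitimate choice.
- **No improper inference is proposed.** Nothing in the article says superiority will be read from differing significance. The example in the working shows a risk left open, not a plan.
- **An unseen analysis plan might add the contrast.** It might, and silence alone would be no finding. But the article does state its contrasts and its sample size basis, and these do not match its own main question.
- **A third primary test would cost power.** Under a Bonferroni split over three contrasts (an assumption; α = 0.0167 each), power at 0.33 SD falls from 80% to about 63% with 18 df. This is a good reason not to make the contrast a third co-primary test.

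**Conclusion.** The point holds as a mismatch between the stated question and the specified analysis. Study aims and Expected results ask about group 2 against group 1; the Abstract, the Background and the analysis section concern each arm against control. The difference of interest is estimable but not specified, so the plan as written yields no test or interval for it.

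The arm-versus-control analyses and their sample size are unaffected, and the 190 per arm reproduces. For group 2 against group 1, that sample gives 80% power only at about 0.33 SD, and 13.6% to 56.5% at differences of 0.10 to 0.25 SD. These figures assume 190 analysed per arm, 10 weeks per arm of equal size, an intraclass correlation of 0.01 and a two-sided 5% test. The differences themselves are assumed. A non-significant head-to-head result would therefore be weak evidence that the two interventions are equivalent.

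**What to change.** 1. Reconcile the aim across the Abstract, Background, Study aims and Expected results. Replace the main research question with explicit contrasts: group 1 vs control, group 2 vs control, and group 2 vs group 1.
2. In the analysis section, pre-specify the group 2 coefficient minus the group 1 coefficient, with its 95% confidence interval from the same hierarchical model, as a key comparison placed after the two arm-versus-control contrasts. Report the estimate and interval whatever the other results.
3. Fix the testing order in advance. For example, leave the two planned contrasts at the α now stated and test group 2 against group 1 only if both are significant. The α and power for arm versus control are then unchanged. The gate can only lower the power for the third contrast below the figures in the working.
4. State that any claim of superiority of group 2 over group 1 will rest on that contrast alone, not on differing significance against control.
5. State that the 80% power refers to arm versus control, and that the difference between groups 2 and 1 detectable with the same power is about 0.33 SD.

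The cost is wording in four sections, one linear contrast from a model already planned, and a narrower power statement. No extra participants are needed.

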**Methods/Design:**

Study participants will be randomly assigned to one of three study arms in five communities in the Bremen-Oldenburg metropolitan region: a) Participants in the first arm will receive access to a web-based intervention for 10 weeks allowing them to track their weekly PA (subjective self-monitoring, intervention group 1); b) participants in the second arm will receive access to the web-based intervention for 10 weeks and, in addition, track PA using Fitbit Zips (objective self-monitoring, intervention group 2); c) participants in the delayed intervention control group will receive access to the intervention implemented in the first study arm after completion of the 12-week follow-up in the other two groups within each community. In addition, weekly group meetings in the communities will be offered to study participants in the intervention groups providing the opportunity to address questions related to the use of the website and to practice PA in groups (e.g., neighborhood walks, strength and balance exercises). To evaluate short-term effects of the intervention on physical and psychological health, PA, physical fitness, and cognitive and psychological variables will be assessed at baseline and 12-week follow-up.

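### The baseline target of 684 leaves about 182 per arm after the assumed 20% loss, not the 190 the article calls necessary

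*Protocol article*

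**What the plan says.** All the figures are in the protocol article, under Quantitative analysis, sample size. The calculation proceeds by "assuming a standardized mean difference of 0.33 in change over time" between each intervention group and the delayed intervention control group, and by "assuming ten clusters (recruitment weeks) per study arm and an intraclass correlation of 0.01". The error rates are "α = 0.05 (two-sided test") and β = 0.20. The result is that "190 participants per study arm will be necessary for the analysis". The next sentence turns this into a recruitment target: "Expecting a loss to follow-up of 20%, we aim for a sample size of" 684, which the article describes as the number "684 at baseline".

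The abstract gives the number of arms: "Study participants will be randomly assigned to one of three study arms". The article states neither the total of 570 nor the formula used to allow for attrition.

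**The concern.** The two sentences do not agree. One gives the number that must remain for analysis, and the other gives a starting number that should yield it after a 20% loss. A loss expressed as a share of those enrolled has to be allowed for by dividing by the retained fraction. Adding 20% to the required number is a common slip and always gives too few, because the loss is taken from the larger enrolled number.

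The primary outcome is the follow-up value minus the baseline value of objectively measured physical activity. A participant lost to follow-up therefore has no observed change score, and the analysed number is what drives power. If the target is wrong, recruitment stops at a number that misses the plan's own requirement even when attrition goes exactly as expected.

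**Working it through.** **Inputs, all from the sample size paragraph except the number of arms (abstract):** standardized difference d = 0.33; k = 10 recruitment weeks per arm; ICC ρ = 0.01; two-sided α = 0.05; power 0.80; 190 per arm for analysis; 20% loss; 684 at baseline; three arms. Equal arms are assumed, as the single per-arm figure implies.

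**Step 1: reproduce the 190.** With n per arm, the mean cluster size is m = n/10 and the design effect is 1 + (m − 1)ρ. The standard error of the standardized difference is √(2 × design effect / n), and the noncentrality is d divided by that standard error.

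- At n = 190: m = 19; design effect = 1 + 18 × 0.01 = 1.18; SE = √(2 × 1.18 / 190) = 0.1114; noncentrality = 0.33 / 0.1114 = 2.961.
- Noncentral t with 2 × (10 − 1) = 18 degrees of freedom (critical value 2.101): power = 79.96%. Power of exactly 80% falls at n = 190.3.
- The normal approximation needs only 166.7 per arm for 80%, so it is not the source of 190.

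The 18-df cluster t-test therefore reproduces 190, and on that basis 190 carries no slack.

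**Step 2: reproduce the 684.**

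- Needed for analysis: 3 × 190 = 570.
- 570 × 1.20 = 684, an exact match.
- 570 / 0.80 = 712.5, which does not match.

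**Step 3: apply the stated loss to the stated target.**

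- 684 × 0.80 = 547.2 in total; 547.2 / 3 = 182.4 per arm.
- Shortfall: 570 − 547.2 = 22.8 in total; 190 − 182.4 = 7.6 per arm.
- Largest loss that 684 can absorb: 1 − 570/684 = 16.7%.
- Baseline number that meets the requirement: 190 / 0.80 = 237.5, so 238 per arm and 714 in total, which is 30 more than 684.

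**Step 4: effect on power at 182.4 per arm.** m = 18.24; design effect = 1.1724; SE = √(2 × 1.1724 / 182.4) = 0.1134; noncentrality = 0.33 / 0.1134 = 2.911.

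| Method | n per arm for 80% power | Power at 190 | Power at 182.4 |
|---|---|---|---|
| t, 18 df (reproduces 190) | 190.3 | 80.0% | 78.6% |
| t, 27 df (three arms, 30 weeks) | 181.8 | 81.4% | 80.1% |
| Normal approximation | 166.7 | 84.2% | 82.9% |

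With 18 df, the difference detectable with 80% power at 182.4 per arm is 0.336 SD.

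**The case against.** The arithmetic of the shortfall is not in dispute. The objection is to what follows from it.

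- **Power depends on the method.** The article states no test and no degrees of freedom. Its planned analysis is one hierarchical model with two treatment dummies over three arms. With ten weeks per arm that gives 30 − 3 = 27 degrees of freedom, and power at 182.4 per arm is then 80.1%. On this view only the count of 190 is missed, not the 80% power. The calculation is correct, and it means a loss of power cannot be asserted without naming the method. It does not rescue the paragraph, however. A 27-df calculation would have asked for 182 per arm and a normal approximation for 167, so neither is the basis of the 190 the article calls necessary.
- **The loss of power is small in any case.** It is 1.4 percentage points, and the model will also include baseline activity and other covariates. Under the 18-df method, covariates explaining about 3.5% of the variance in change would restore 80%, since 1 − (0.330/0.336)² ≈ 0.035. The true share is not in the document. This stands as a comment on practical importance.
- **The multiplication by 1.2 is inferred.** The formula is not printed. This stands too, but the match is exact, and the shortfall follows from the printed figures whatever formula was used.

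No reading of the text makes 684 consistent. The number is given for baseline and the 20% as loss to follow-up, so the loss is a share of those enrolled. A gap of about 23 analysed participants is not rounding.

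**Conclusion.** The concern holds. On the article's own figures, 684 at baseline with 20% loss gives about 182 per arm, against a stated need of 190. This rests only on three equal arms, and even without equal arms the total of 547 is below 570.

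The consequence for power is minor: 78.6% instead of 80.0%, assuming the 18-df cluster t-test that reproduces 190. No test, analysis population or outcome definition is affected, and the trial's validity is not at risk. It is nevertheless an error in a printed figure that recruitment works towards, and nothing else in the article reconciles it.

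**What to change.** Correct the attrition sentence in one of two ways.

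- **Keep 684.** State that a 20% loss leaves about 182 per arm, with about 78.6% power for a difference of 0.33 SD (cluster t-test, 18 df), or that the design allows a loss of up to 16.7%. This costs one sentence, no extra participants and a slightly less favourable power figure.
- **Keep 190 per arm and 20% loss.** Set the baseline target at 714 (238 per arm). This costs 30 more participants, an average of 23.8 per recruitment week instead of 22.8. The sponsor would need to confirm that this is feasible.

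The first option is sufficient. With either, the sentence should name the test and degrees of freedom behind the 190, so that the power figure can be checked.

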#### Qualitative analysis

Qualitative focus group discussions (eight groups) will be protocolled by two researchers and audio-recorded. The aim of these focus groups discussions will be to assess the usability of the web-based intervention with subjective and objective PA monitoring (intervention group 2). Results of these focus groups will form the basis for improving interventions in the future, particularly for different user groups (e.g., females). Audio-records will be transcribed and records will be compared and complemented by analyzing the protocols. Both, deductive and inductive methods will be used for analyzing the data based on Mayring [46].

